**Evaluation of non-target lesions**

|                                                      |                                                                                                                  |
|------------------------------------------------------|------------------------------------------------------------------------------------------------------------------|
| Complete Response (CR):                       | Disappearance of all non-target lesions and normalization of tumor marker level                                  |
| Incomplete Response/
Stable Disease (SD): | Persistence of one or more non-target lesion(s) or/and maintenance of tumor marker level above the normal limits |
| Progressive Disease (PD):                     | Appearance of one or more new lesions and/or unequivocal progression of existing non-target lesions (1)          |

(1) Although a clear progression of "non target" lesions only is exceptional, in such circumstances, the opinion of the treating physician should prevail and the progression status should be confirmed later on by the review panel (or study chair).

**Evaluation of best overall response**

The best overall response is the best response recorded from the start of the treatment until disease progression/recurrence (taking as reference for PD the smallest measurements recorded since the treatment started). In general, the patient's best response assignment will depend on the achievement of both measurement and confirmation criteria

| Target lesions | Non-Target lesions     | Evaluation of non-target lesions | Overall response |
|----------------|------------------------|----------------------------------|------------------|
| CR             | CR                     | No                               | CR               |
| CR             | Incomplete response/SD | No                               | PR               |
| PR             | Non-PD                 | No                               | PR               |
| SD             | Non-PD                 | No                               | SD               |
| PD             | Any                    | Yes or No                        | PD               |
| Any            | PD                     | Yes or No                        | PD               |
| Any            | Any                    | Yes                              | PD               |

- Patients with a global deterioration of health status requiring discontinuation of treatment without objective evidence of disease progression at that time should be classified as having "symptomatic deterioration". Every effort should be made to document the objective progression even after discontinuation of treatment.
- In some circumstances it may be difficult to distinguish residual disease from normal tissue. When the evaluation of complete response depends on this determination, it is recommended that the residual lesion be investigated (fine needle aspirate/biopsy) to confirm the complete response status.

---

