#### **4.7 CRITERIA FOR STOPPING TREATMENT**

Protocol treatment may be stopped in the following instances:

- Evidence of progressive disease according to RECIST criteria on CT scan (appendix 4)
- Unacceptable toxicity
- An early toxicity assessment (after 20 patients have completed treatment in each arm) for safety reasons will be carried out. Data will be reviewed by the TMG.
- Intercurrent illness which, in the clinician's opinion, would require discontinuation of protocol therapy.
- If subsequent histological/cytological review is contrary to the original diagnosis
- Patient's request

For patients with measurable disease, evidence of minor disease progression (stable disease by RECIST criteria) is not a requirement to stop treatment in an otherwise clinically and symptomatically stable patient.

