### 7.3.2 Qualifications for Analysis of Tumour Response

All patients meeting the following criteria will be evaluated for tumour response and included in the analysis of tumour response rates:

- treatment with at least one dose of cisplatin and etoposide.

**Response** will be assessed according to RECIST criteria (appendix 4) and the proportion of patients in each treatment group whose best response up to, approximately 28 days post cycle 4 or, if stopped prior to cycle 4, approximately 28 days after last chemotherapy cycle given, from randomisation is complete or partial will be compared using Chi-squared and Fisher Exact tests.

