**Baseline documentation of "Target" and "Non-Target" lesions**

- All measurable lesions up to a maximum of five lesions per organ and 10 lesions in total, representative of all involved organs should be identified as **target lesions** and recorded and measured at baseline.
- Target lesions should be selected on the basis of their size (lesions with the longest diameter) and their suitability for accurate repeated measurements (either by imaging techniques or clinically).
- A sum of the longest diameter (LD) for *all target lesions* will be calculated and reported as the baseline sum LD. The baseline sum LD will be used as reference by which to characterize the objective tumor.
- All other lesions (or sites of disease) should be identified as **non-target lesions** and should also be recorded at baseline. Measurements of these lesions are not required, but the presence or absence of each should be noted throughout follow-up.

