**Response Criteria****Evaluation of target lesions**

|                                  |                                                                                                                                                                                           |
|----------------------------------|-------------------------------------------------------------------------------------------------------------------------------------------------------------------------------------------|
| Complete Response (CR):   | Disappearance of all target lesions                                                                                                                                                       |
| Partial Response (PR):    | At least a 30% decrease in the sum of the LD of target lesions, taking as reference the baseline sum LD                                                                                   |
| Progressive Disease (PD): | At least a 20% increase in the sum of the LD of target lesions, taking as reference the smallest sum LD recorded since the treatment started or the appearance of one or more new lesions |
| Stable Disease (SD):      | Neither sufficient shrinkage to qualify for PR nor sufficient increase to qualify for PD, taking as reference the smallest sum LD since the treatment started                             |

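### Appendix 4 mislabels what should be the new-lesions column of its best-overall-response table; read literally, patients with evaluated non-target lesions would be classed as progressive

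*Supplement*

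**What the plan says.** Protocol Section 7.3.2 states that response "will be assessed according to RECIST criteria (appendix 4) and the proportion of patients in each treatment group whose best response", within a set window, is complete or partial will be compared by chi-squared and Fisher exact tests. The SAP repeats that comparison. It names RECIST but cites neither Appendix 4 nor its table.

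Appendix 4 has three tables that matter here.

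- **Target lesions.** Progression is a 20% increase in the sum of longest diameters "or the appearance of one or more new lesions".
- **Non-target lesions.** Progression is "Appearance of one or more new lesions and/or unequivocal progression of existing non-target lesions".
- **Best overall response.** Target status, non-target status and a Yes/No column are combined into an overall category. The heads of the last two columns are "Evaluation of non-target lesions | Overall response". No column is headed new lesions.

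The appendix also says of non-target lesions that "the presence or absence of each should be noted throughout follow-up". The same column head stands in the earlier protocol version in the supplement, and the records of changes do not touch it. Section 4.7 cites Appendix 4 as well, for progressive disease as an instance in which protocol treatment may be stopped.

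**The concern.** The heading makes the deciding Yes/No input a matter of whether an assessment was done, not of what it showed. Every row that yields complete response, partial response or stable disease requires No, and the last row turns any Yes into progression. Non-target lesions are meant to be followed throughout, so a site that complied and took the heading at its word would enter Yes for anyone with non-target disease and would record progression whatever the tumour did.

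The table is the only written algorithm in the documents for turning lesion readings into an overall category. If some sites or programs followed the heading and others followed standard practice, patients with the same scans would be classified differently. The complete-plus-partial proportion tested between the arms would then contain error unrelated to treatment.

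**Working it through.** The plan gives no figure to reproduce; the check is of a decision table against the definitions printed just before it.

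**Step 1: the rules.** The seven rows of the best-overall-response table are:

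| Target | Non-target | Third column | Overall |
|---|---|---|---|
| CR | CR | No | CR |
| CR | Incomplete/SD | No | PR |
| PR | Non-PD | No | PR |
| SD | Non-PD | No | SD |
| PD | Any | Either | PD |
| Any | PD | Either | PD |
| Any | Any | Yes | PD |

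**Step 2: enumeration.** Four target statuses times three non-target statuses (CR, incomplete/SD, PD) give 12 combinations.

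- Third column Yes: 12 of 12 give PD, including target CR with non-target CR.
- Third column No: 1 gives CR, 3 give PR, 2 give SD and 6 give PD (1 + 3 + 2 + 6 = 12).

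**Step 3: which meaning of the column is coherent?**

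- *Whether non-target lesions were evaluated (the heading as printed).* The first four rows need a non-target result in a patient whose non-target lesions were not evaluated, so they contradict themselves. The last row overrides the non-target table, which defines complete response and stable disease for lesions that have been assessed.
- *Whether new lesions appeared.* Each of the 12 combinations has one result under No. Yes always gives PD, as the target and non-target definitions require. All seven rows make sense.

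Only the second meaning agrees with the rest of the appendix.

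**Step 4: do new lesions depend on this column?** No. A new lesion makes target status PD under the target definition and non-target status PD under the non-target definition. Both enter through the rows PD/Any and Any/PD, which give PD whether the third column is Yes or No.

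**Step 5: effect of the literal reading on the comparison.** Let p₁ and p₂ be the true response proportions in the two arms. Let s be the share of patients whose non-target lesions are evaluated and who are therefore coded PD. Assume that s is the same in both arms and unrelated to response, and that the remaining patients are classified correctly. The observed proportions are (1 − s)p₁ and (1 − s)p₂, and their difference is (1 − s)(p₂ − p₁). The difference shrinks as s grows and vanishes only at s = 1. The documents give neither s nor any expected response rate, so the loss cannot be put into numbers.

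**The case against.** The strongest reply is that nobody could work with the literal reading. It contradicts the table's own response rows, and the heading repeats the title of the non-target table just above, as a copying slip would. An experienced RECIST reader would probably see through it, the appendix cites its source, and an output with no responders among evaluated patients would give the error away. New lesions reach progression without the column. The SAP relies on RECIST by name and not on this table, and Section 4.7 needs a definition of progression, which the two definition tables supply.

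Most of this stands, and it limits the consequence. It does not make the heading right. Section 7.3.2 cites the appendix by number, and a derivation table for a multicentre trial should not depend on readers ignoring its heading.

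It may also be said that the heading is an artefact of reading the PDF, since other tables in the same protocol version came through with displaced columns. That cannot be fully excluded, because both versions were read the same way. The identical heading in two separate versions makes it unlikely.

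**Conclusion.** The point holds as a minor labelling error. The third column of the best-overall-response table carries the wrong heading on the appendix's own terms, and its entries are coherent only as a record of new lesions. Taken literally, it would class every patient with evaluated non-target lesions as progressive and so misclassify response.

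A reader might infer that the response comparison therefore cannot discriminate between the arms. The documents do not support that. Patients without evaluated non-target lesions could still be counted as responders, so the effect is dilution unless every patient is affected, and that share is not given. Nor do the documents show that any site or program applied the heading literally.

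The reach is limited as well. Tumour response is compared between arms but is not a listed primary or secondary endpoint. Overall survival is unaffected. Local progression-free survival is defined by clinical evidence of progression at the primary site or death, not by this table. The conclusion assumes that the heading in the supplement is the one in the protocol.

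**What to change.** In Appendix 4, relabel the third column of the best-overall-response table *New lesions (Yes/No)*, so that it matches the two definitions of progression before it. Cite the corrected table in the SAP's response paragraph. Confirm that responses already recorded, and the derivation program, were based on new lesions and not on whether non-target lesions had been evaluated. Because Section 4.7 relies on the same appendix for progressive disease, the table and the definitions must be reconciled for that use too; no change to the clinical rule is proposed here.

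The cost is one column heading, one cross-reference in the SAP, a note to sites and a check of the program and recorded responses. No new data and no additional patients are needed.

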**APPENDIX 5****COCKCROFT & GAULT FORMULA**

---

**If creatinine measured in µmol/l:**

**Males:** 
$$\frac{1.23 \times (140 - \text{age}) \times \text{weight(kg)}}{\text{serum creatinine (µmol/l)}}$$

**Females:** 
$$\frac{1.05 \times (140 - \text{age}) \times \text{weight(kg)}}{\text{serum creatinine (µmol/l)}}$$

**If creatinine measured in mg/%**

**Males:** 
$$\frac{(140 - \text{age}) \times \text{wt (kg)}}{72 \times \text{serum creatinine}}$$

**Females:** 
$$\frac{(140 - \text{age}) \times \text{wt (kg)} \times 0.85}{72 \times \text{serum creatinine}}$$

**APPENDIX 6****SUGGESTED SCHEME FOR ADMINISTRATION OF CHEMOTHERAPY CYCLES**

---

**Etoposide and Cisplatin every 21 days for 4-6 cycles****Etoposide**

100 mg/m^2 days 1-3 BSA daily administered as an intravenous infusion over 1 hour every 3 weeks

**Cisplatin**

75 mg/m^2 day 1 or 25 mg/m^2 days 1-3 BSA administered as an intravenous infusion over 2 hours every 3 weeks

**OPTION 1: Cisplatin given on day 1 only****Day 1**

*Administer anti-emetics according to local guidelines*

| Time                          | Drug                    | Fluid                                                                         |
|--------------------------------------|--------------------------------|--------------------------------------------------------------------------------------|
| 0.00                                 | -                              | 1 litre 0.9% sodium chloride over 2 hours with 20 mmol of KCl                        |
| When urine output $\geq$ 100ml/hour: |                                |                                                                                      |
| 2.00                                 | cisplatin 75mg/m   | Given in 1 litre normal saline with 1g MgCl 20mmol over 2 hours                      |
| 4.00                                 | Etoposide 100mg/m  | 1 litre 0.9% sodium chloride over 1 hour                                             |
| 5.30                                 | Post – cisplatin hydration     | 1 litre iv normal saline with KCl 20mmol and magnesium sulphate 10 mmol over 2 hours |

*Maintain oral intake of 1-2 litres of fluid for 6 hours after iv fluids discontinued.*

**Days 2 and 3**

*Administer anti-emetics according to local guidelines.*

|      |                                 |                                          |
|------|---------------------------------|------------------------------------------|
| 0.00 | Etoposide 100 mg/m  | 1 litre 0.9% sodium chloride over 1 hour |
|------|---------------------------------|------------------------------------------|

**OPTION 2: Cisplatin given day 1 to 3****Days 1-3**

| Time | Drug                          | Fluid                    |
|-------------|--------------------------------------|---------------------------------|
| 0.00        | Cisplatin 25 mg/m  d1-3  | 500ml normal saline over 1 hour |
| 1.00        | Etoposide 100 mg/m  d1-3 | 500ml normal saline over 1 hour |

*Patients to have an oral intake of 2 litres of fluid days 1 to 3*

## APPENDIX 7

**CHEMOTHERAPY AGENTS - safety profiles**

---

**Etoposide** - <http://emc.medicines.org.uk> (as per SmPC)

**Safety profile**

The main toxicities associated with etoposide are:

**Gastrointestinal toxicity:** Nausea and vomiting are the major gastro-intestinal toxicities. The severity of such nausea and vomiting is generally mild to moderate with treatment discontinuation required in 1% of patients. Diarrhoea, anorexia and mucositis may occur. Constipation and swallowing disorder have been observed rarely.

**Haematotoxicity:** Myelosuppression is dose limiting, with granulocyte nadirs occurring 5 to 15 days after drug administration and platelet nadirs occurring 9 to 16 days after drug administration. Bone marrow recovery is usually complete by day 21, and no cumulative toxicity has been reported.

**Allergic reactions:** Seldom hypersensitivity reactions caused by benzyl alcohol may occur. Anaphylactic-like reactions characterised by flushing, tachycardia, bronchospasm, and hypotension have been reported (incidence 0.7-2%), also apnoea followed by spontaneous recurrence of breathing after withdrawal of etoposide infusion, increase in blood pressure. The reactions can be managed by cessation of the infusion and administration of pressor agents, corticosteroids, antihistamines and/or volume expanders as appropriate.

**Hypotension:** Transient hypotension following rapid intravenous administration has been reported in 1% to 2% of patients. It has not been associated with cardiac toxicity or electrocardiographic changes. To prevent this rare occurrence, it is recommended that etoposide is administered by slow intravenous infusion over a 30- to 60-minute period. If hypotension occurs, it usually responds to supportive therapy after cessation of the administration. When restarting the infusion, a slower administration rate should be used.

**Other toxicities:** Reversible alopecia, sometimes progressing to total baldness was observed in up to 70% of patients. The following adverse reactions have been infrequently reported: peripheral neuropathy, paresthesia, increased liver function tests with high doses, radiation "recall" dermatitis, hand-foot syndrome, central nervous effects (fatigue, drowsiness) 0-3%, hyperuricemia, taste impairment, fever, rash, urticaria, skin discoloration, pruritus, abdominal pain. The following adverse events have been reported after administration of etoposide (a causal relationship has not been established): Stevens-Johnson syndrome, rhythm disorders, myocardial infarction, reversible loss of vision.

**Cisplatin** - <http://emc.medicines.org.uk> (as per SmPC)

**Safety profile**

The main toxicities associated with cisplatin are:

**Nephrotoxicity:** Renal toxicity has been noted in about one third of patients given a single dose of cisplatin when prior hydration has not been employed. It is first noted during the second week after a dose and is manifested by elevations in plasma urea and serum creatinine, serum uric acid and/or decrease in creatinine clearance.

Renal toxicity becomes more prolonged and severe with repeated courses of the drug. Renal function must return to acceptable levels before another dose of cisplatin can be given.

Renal function impairment has been associated with renal tubular damage. The administration of cisplatin using a 6-8 hour infusion with intravenous hydration and mannitol has been used to reduce nephrotoxicity. However renal toxicity still can occur after utilisation of these procedures.

**Gastrointestinal toxicity:** Nausea and vomiting occur in the majority of patients, usually starting within 1 hour of treatment and lasting up to 24 hours. Anorexia, nausea and occasional vomiting may persist for up to a week.

**Ocular toxicity:** There have been reports of optic neuritis, papilloedema and cerebral blindness following treatment with cisplatin. Improvement and/or total recovery usually occurs following immediate discontinuation. Blurred vision and altered colour perception have been reported after the use of regimens with higher doses of cisplatin or greater dose frequencies than those recommended.

**Ototoxicity:** Ototoxicity has occurred in up to 31% of patients treated with a single dose of cisplatin 50 mg/m^2. Ototoxicity may be more severe in children and more frequent and severe with repeated doses.

Careful monitoring should be performed prior to initiation of therapy and prior to subsequent doses of cisplatin.

Unilateral or bilateral tinnitus, which is usually reversible, and/or hearing loss in the high frequency range may occur.

The overall incidence of audiogram abnormalities is 24%, but large variations exist. These abnormalities usually appear within 4 days after drug administration and consist of at least a 15 decibel loss in pure tone threshold. The damage seems to be cumulative and is not reversible. The audiogram abnormalities are most common in the 4000-8000 Hz frequencies.

**Haematotoxicity:** Myelosuppression is observed in about 30% of patients treated with cisplatin. Leucopenia and thrombocytopenia are more pronounced at higher doses. The nadirs in circulating platelets and leucocytes generally occur between days 18-23 (range 7.3 to 45) with most patients recovering by day 39 (range 13 to 62). Leucopenia and thrombocytopenia are more pronounced at doses greater than 50 mg/m^2. Anaemia (decreases of greater than 2 g% haemoglobin) occurs at approximately the same frequency, but generally with a later onset than leucopenia and thrombocytopenia. Subsequent courses of cisplatin should not be instituted until platelets are present at levels greater than 100,000/mm^2 and white cells greater than 4,000/mm^2. A high incidence of severe anaemia (range 9-40%) requiring transfusion of packed red cells has been observed in patients receiving combination chemotherapy including cisplatin.

**Anaphylaxis:** Reactions possibly secondary to cisplatin therapy have been occasionally reported in patients who were previously exposed to cisplatin. Patients who are particularly at risk are those with a prior history or family history of atopy. Facial oedema, wheezing, tachycardia, hypotension and skin rashes of urticarial non-specific maculopapular type can occur within a few minutes of administration. Serious reactions seem to be controlled by IV adrenaline, corticosteroids or antihistamines.

**Serum electrolyte disturbances:** Hypomagnesaemia, hypocalcaemia, hyponatremia, hypokalemia and hypophosphatemia have been reported to occur in patients treated with cisplatin and are probably related to renal tubular damage. Hypomagnesaemia and hypocalcaemia may result in tetany. Generally, normal serum electrolyte levels are restored by administering supplemental electrolytes and discontinuing cisplatin. Inappropriate antidiuretic hormone syndrome has also been reported.

**Neurotoxicity:** Usually characterised by peripheral neuropathies and paresthesia in both upper and lower extremities. Peripheral neuropathy, while reversible, may take a year or more to recover. Loss of taste and seizures have also been reported. Neuropathies resulting from cisplatin treatment may occur after prolonged therapy; however, neurological symptoms have been reported to occur after a single dose. The neuropathy may progress after stopping treatment.

**Hyperuricemia:** Hyperuricemia occurring with cisplatin is more pronounced with doses greater than 50 mg/m^2. Allopurinol effectively reduces uric acid levels.

**Other toxicities:** Vascular toxicities coincident with the use of cisplatin in combination with other antineoplastic agents have been reported rarely. These events may include myocardial infarction, cerebrovascular accident, thrombotic microangiopathy (haemolytic uraemic syndrome) or cerebral arteritis. There are also reports of Raynaud's phenomenon occurring in patients treated with the combination of bleomycin, vinblastine with or without cisplatin. It has been suggested that hypomagnesaemia developing coincident with the use of cisplatin may be an added, although not essential factor, associated with this event. However the cause of this Raynaud's phenomenon is currently unknown.

Other toxicities reported to occur infrequently are cardiac abnormalities including tachycardia, postural hypotension and arrhythmia.

Local soft tissue toxicity has been reported rarely following extravasation of cisplatin. Infiltration of solutions of cisplatin may result in tissue cellulitis, fibrosis and necrosis.

**Carboplatin** - <http://emc.medicines.org.uk> (as per SmPC)

